## Methods

The trial will follow the consolidated standards of reporting trials statement [57].

### Trial design

This study is a two-arm, parallel design, single blinded randomized controlled trial (RCT). Participants (mothers and fathers) are randomized to one of two groups 1) physical activity theory-based condition; or 2) standard attention control condition for 6 months duration post parenthood onset (baseline assessment at 2 months postpartum and final follow-up at 8 months postpartum). The trial is registered with the National Library of Medicine at the National Institutes of Health and was registered on April 19, 2014. The registration ID is NCT02290808. We obtained ethical approval from the University of Victoria Human Research Ethics Board and all amendments to the study went through the Human Research Ethics Board.

### Participants and recruitment procedure

Participants are common law or married couples, who reside in greater Victoria, British Columbia and who are expecting or have just had their first child and are over the age of 18 years. Single parents are no doubt an interesting group for study with physical activity, but they will be excluded from this study because the intervention is targeting the couple. Same sex parents and surrogate parents are included in the study if their baby is within four-months of birth. Our prior longitudinal studies also included same sex couples, although this accounted for less than 1% of the sample [52]. Parents are included if they participate in physical activity below or above Canadian recommended guidelines [62] (i.e., 150 min of moderate or higher intensity activity per week). While many intervention studies often seek to screen out active participants in order to create change in physical activity, new parents represent a group where 50% who were previously meeting physical activity guidelines, will no longer be active at this level [37]. Our intervention is focused on both preventing that decline and improving physical activity. As a result, we are recruiting couples who are both active or inactive. Participants are screened for physical activity readiness via the Physical Activity Readiness Questionnaire for Everyone (PAR-Q+; www.eparmedx.com) [66, 67]. Those individuals who are not ready or able to participate in moderate intensity physical activity are excluded for safety reasons. This may include complicated pregnancy, caesarean section or any previous injuries in potential participants. Mental health conditions such as depression or anxiety are not contraindications to beginning a physical activity program [55], and therefore participants are not excluded if they have a mental health condition. However, we are measuring psychological distress and mental health among participants and are examining the impact this condition may have on retention and program success.

### Recruitment

Recruitment has already started and we are continuing to recruit through several clinical and community avenues including the utilization of online platforms, print campaigns, in-person recruitment, as well as on a referral basis. Study announcements outlining the research are posted to online interest sites, where they are marketed to the target demographic. Paper advertisements are distributed systematically around the city, focusing on doctor’s offices, health centers, midwiferies, recreation centers, maternity and baby stores, and any other community organizations offering prenatal classes or programming for first-time parents. Potential participants recruited via online or print methods are invited to contact the project coordinator and research assistants associated with this project, who act as the main point of contact. In-person recruitment initiatives take place at community fairs targeting new parents such as baby fairs, health shows, and community markets. At these events, brochures outlining the research are distributed. The research assistant is also available to answer any questions about the study, as well as to speak to the importance of being physically active postpartum. The research assistant then invites interested attendees to participate in the research study. A sign-up sheet is distributed for those interested in participating (provide their name, home/cell phone number, email, expected due date). Lastly, enrolled participants are invited to refer other families that may be interested in participating.

### Procedures

After interested participants contact the research assistant and are determined to be eligible to participate in the study, (and provide an approximate date for contact 2 months post-baby) we schedule a fitness test at our lab. At the initial visit to the lab, signed informed consent is obtained from participants by the project coordinator after overviewing the requirements of the study. Participants are assigned an identification number and all data is attached to this number to ensure confidentiality. A qualified exercise professional is employed to ensure consistency of the fitness testing procedures [68] and is also present at the first initial meeting. This individual is responsible for quality control throughout the fitness-testing portion of the trial. The fitness testers are blind to the treatment conditions of the participants. Both parents are given accelerometers to wear for 1 week and instructed on how to enter information about each day’s activity in a log. Fitness testers provide a short training session on how to wear and use the accelerometers. After the 1 week wear of accelerometers, participants are randomized at a 1:1 ratio to either intervention or control group, using an online randomizer program. Participants as well as the research assistants and project coordinator are aware of the group allocations, but all fitness testers are blinded to treatment allocation. The project coordinator and research assistants have to be aware of the condition to which participants are randomized in order to deliver the appropriate materials. The project coordinator and research assistant meet with participants at their home or location of choice to go through their specific intervention materials. Two people attend the house visits for safety reasons.

After the initial 6 week intervention period, couples are given online follow-up questionnaires sent via email to complete and accelerometers are dropped off to their house to be worn for another week and then are picked up by the research assistant. Contact is made initially with a phone call by the research assistant to setup a meeting time with participants and to prime them for the emailed online questionnaire. Both groups receive a site “booster” session on the same material but the intervention group focuses on revisiting their experiences over the past six-weeks and re-set goals and redefine/problem-solve obstacles. Participants in the control group receive a booster session but this is more of a general check in. The same protocol is followed at the 3 month time period. Thus, two booster sessions (six-weeks, 3 months) are provided to all participants. At 6 months follow-up (i.e., 8 months post-baby), parents are asked to return to the lab to complete a brief questionnaire, perform the final fitness test and participate in a brief end-of-trial quantitative questionnaire and qualitative interview to evaluate the impact of the intervention and usefulness of the intervention material. To gain a better understanding of the factors associated with physical activity we conduct semi-structured interviews with parents, in order to examine both *content fidelity* (“what is done”) and *process fidelity* (“how it is done”) related to the delivery of the intervention trial [18]. Although quantitative measurement of outcomes will enable us to examine the potency of our intervention, a process evaluation (whereby participants are interviewed) is also essential to examine the *extent to which the* program is delivered and implemented as planned.

To help study retention, we offer monetary compensation in the form of grocery store gift cards ($25 per participant, increasing by $5 each assessment) across the study.

### Intervention

Couples randomized to the intervention condition receive a post-baby physical activity workbook that serves as the template for a dialogue with the research assistant for the study. The intervention booklet was informed by the Theory of Planned Behavior (TPB) concepts and preliminary results of our prior trials [42], as well as the components that have been successful in prior intervention research with mothers and couple-based health interventions [10, 11, 17, 21, 22, 34, 37]. The booklet consists of two main sections. Physical activity guidelines are presented in the introductory section of the guide in order to define what is meant by regular physical activity and set the behavioral context. The first section focuses on the benefits of post-partum physical activity on immune function, a better night’s sleep, increase in overall energy levels, control of food cravings, reduction of pain, and finally prevention and treatment of baby blues. This section is intended to target our prior findings where affective attitudes and the belief that regular physical activity can reduce stress predicted those parents who were active from those who were not. The section concludes with a brainstorming exercise for couples where they list physical activities that they have found fun in the past, activities that may be enjoyable with their new baby, and activities that they might find enjoyable to do together. This brainstormed list helps create the template for physical activity planning/problem solving in the second section by contextualizing what the participants would like to do.

The second section guides participants through the process of finding time and planning for postpartum physical activity as well as identifying barriers and strategies to meet recommended guidelines via self-regulatory approaches [28, 52, 59] both personally and as a couple. Participants brainstorm a list of potential and past barriers (and then strategies to overcome these) when setting their physical activity goals. This section is intended to target the control barriers of regular physical activity that were identified in our prior research on parents and to improve self-regulatory strategies. The content addresses social support strategies as a couple, with friends/or extended family, problem solving around bad weather, and low-cost activities as well as coping with fatigue. The section concludes with a discussion of a re-set day (often Sunday) where the couple can reorganize their physical activity goals and plans for the following week and reflect on what “worked” and what “didn’t work” from the previous week. The emphasis is placed on how the couple can support each other to overcome barriers to physical activity either by sharing responsibilities or doing more activity together. For an outline of the study materials, please see the Additional file 1 and for an outline of the consent form please see Additional file 2. The two booster sessions (6 weeks and 3 months) serve to re-open the dialogue and assess how the couple is proceeding with in-person meetings between the couple and the research assistant. The benefits of physical activity, enjoyable activities to do, and goal setting and problem solving between the participants is re-explored and alternative plans and solutions are discussed if needed.

Couples in the control group receive physical activity guidelines and verbal presentation on the importance of physical activity post-partum. More specifically, fathers in the control condition receive the Recommendations for Physical Activity for Adults recommending 150 min of activity per week in bouts of 10 min and additional recommendations and guidelines about intensity, frequency and duration as well as ways to meet the recommended physical activity guidelines through structured and unstructured, and endurance and strength activities. Mothers in the control condition receive a comparable guide, entitled *Post-partum Physical Activity Guidelines,* which has relatively similar content. Mothers are also advised to incorporate kegel, core, and strengthening exercises into their routine.

### Outcome measures

#### Primary outcome measure:

*Change in Objective and Self-reported Physical Activity* Physical activity is measured objectively for seven consecutive days using the GT1M Activity Monitor at each time period (baseline, 6 weeks, 3 months, 6 months). It is designed to ascertain normal human movement without impeding activity and has been shown to provide valid and reliable estimates of physical activity [31]. Seven days has been proposed as an appropriate number of days for wearing a physical activity monitor to reliably estimate habitual physical activity [36, 63]. This length of time also aligns with validated self-report measures such as the Godin Leisure Time Exercise Questionnaire (GLTEQ) [26] and Physical Activity Recall (PAR) [56] as well as national physical activity recommended guidelines, all of which use a 7 day reference period [62]. The activity monitor is attached to an elastic belt and worn at the waist above the left hip. Best practice recommendations for accelerometry wear time suggest choosing a length of time that is sufficient to capture habitual physical activity while not becoming overly burdensome on participants or study resources [36]. Participants are instructed to wear the monitor from when they get up in the morning to when they go to bed and for at least 10 h and to remove the monitors at night and while swimming, bathing, or showering. Participants also complete a daily log / diary that identifies when the accelerometer is removed, unusual circumstances and structured activities.

Both acceleration and step-count are obtained using the monitor. Physical activity is assessed by measuring duration (total minutes worn, total movement counts/day, total minutes of sedentary, moderate-vigorous, and vigorous activity/day), frequency (bouts of sedentary, moderate-vigorous, and vigorous activity/day), and intensity. To calculate these variables the monitor is programmed to store data at 10 s intervals on each day.

As a secondary physical activity outcome, we use a self-report measure with the modified Godin Leisure-Time Exercise Questionnaire (GLTEQ) [26] asked at all four time points. The GLTEQ contains three questions, which assess the frequency of mild, moderate, and strenuous activity performed for at least 15 min of duration during free time in a typical week. A total GLTEQ score will be calculated by adding the frequency of physical activity within the moderate, and strenuous categories. An independent evaluation of this measure found its reliability and validity to compare favourably to nine other self-report measures of exercise based on various criteria including test-retest scores, objective activity monitors, and fitness indices [30].

#### Secondary outcome measures:

Motivation for physical activity is measured using the constructs of the theory of planned behavior and self-regulation strategies. These have been validated in parent populations [49, 50]. Items will measure all components of the model (affective attitude, instrumental attitude, injunctive norm, descriptive norm, perceived control, planning) including behavioral, normative, and control beliefs developed from prior pilot work in parents [37]. Five items are used to assess affective attitude and instrumental attitude and are measured on a 5 pt. scale. The items ask parents about their beliefs regarding physical activity behaviour over the next 6 weeks (i.e. “Over the next six weeks, engaging in physical activity on a regular basis would be … 1) Extremely unenjoyable to 5) extremely enjoyable”). Three items are used to measure subjective norms on a 5-point scale ranging from strongly disagree to strongly agree. Three items measuring perceived control are used to assess participants’ confidence that they can be regularly active over the next 6 weeks on a 5-point scale (strongly disagree to strongly agree). Intentions are measured with two items with 5-point scales (i.e. “Over the next six weeks, I am motivated to be physically active on a regular basis, and 2) Over the next six weeks I am determined to be physically active on a regular basis”). Control beliefs over perceived barriers are measured by asking participants to select the importance of each factor in preventing them from participating in 150 min of moderate to vigorous physical activity per week. Possible barriers include items such as family activities, work, mood, stress etc. Participants answer on a 5-point scale from “1) Does not prevent me at all, to 5) Prevents me a great deal”). The self-regulation items have been adapted from other sources [59, 64] and included 8 items to be answered on a 5 point scale from “Never” to “Very often”. For example, questions include items such as, “Over the past 6 weeks, I kept track of my physical activity in a diary or log”, and “Over the past 6 weeks, I set short-term (daily or weekly) goals for leisure-time physical activity.”

##### Musculoskeletal fitness

Grip strength, push ups, sit & reach flexibility, partial curl-ups, vertical jump, and back extension will be measured to determine the musculoskeletal fitness of both the children and parents using the procedures established by Gledhill and Jamnik [25] Change in musculoskeletal fitness from baseline to 6 months (i.e., post-intervention) will be examined.

##### Demographics

A brief section in the baseline questionnaire assesses characteristics including age, gender, marital status, ethnicity, level of education, health background, employment information, sleep, smoking behaviour, alcohol drinking and general eating behaviours.

##### Evaluation of intervention

A brief end-of-program interview is conducted for two main purposes. The first is to gain a deeper understanding of parent’s attitudes towards physical activity and to provide them with an opportunity to expand verbally on their experiences. Questions will include asking parents to talk about how their lifestyle was before the birth of their child to afterwards, if their physical activity has changed and what barriers they faced over the duration of the study. The second part of the interview will endeavor to determine how parents perceived the intervention materials and the delivery of the materials. Fidelity questions will be guided by the key points discussed in the article by Dumas et al. [18]. For example, questions will aim to ensure the intervention was delivered as designed, that the delivery did not change throughout the study, that it was delivered with consistency and with effective communication across the duration of the study and that participants adhered to their particular condition. Six questions pertaining to intervention fidelity will be included in the interview including, “Did you feel the information provided to you in the workbook and from the meetings with the research assistant helped to increase your physical activity?”, “Did you find the meeting sessions with the research investigator useful?”, “Have you been able to incorporate the strategies provided in the workbook and the ones you brainstormed during the meeting sessions?”, “Do you have any suggestions as to how the workbook or mini counseling sessions could be more useful for helping you increase your physical activity?”, “Did you find the check-in sessions helped you both work together to come up with a plan to increase your physical activity?”, and “Did you find the information and check-in sessions helped you both to work together to increase your physical activity?”.

### Analysis strategy

Missing data will be evaluated for patterns of missingness for each psychosocial variable and behavior at all time points using the dummy coding procedures of Allison [2]. Depending on the outcome of these tests (e.g., missing at random, missing completely at random, etc.) we will initiate the appropriate missing data handling strategy. Intention to treat analyses will also be performed in addition to sensitivity analysis procedures. An assessment of covariates will also be performed. As one would expect during early parenthood many factors may contribute to inactivity which include but are not limited to child care status, leave status, baseline quality of life and other general demographics. The RCT approach aids in some equalization in the group x time effect of these factors, yet it is acknowledged that some of these confounds may affect the time effect regardless of randomisation.

To address the first objective, hierarchical linear modeling will be used in HLM 6.0. First, a Level-1 no intercept model will be specified such that a main effect will be entered for father (0 = Mother; 1 = Father), Mother (0 = Father; 1 = Mother), a Father linear trend (0 = baseline; 1 = 6 months), and a Mother linear trend with all coefficients set to random. In this model, the main effects for the fathers and mothers’ intercepts represent their respective baseline minutes of MVPA, whereas the linear trends represent the change in MVPA (or not) over the 6-month interval. At Level-2, cross-level interactions will be added such that condition (0 = control; 1 = intervention) predicts the fathers’ Level-1 intercept / slope and the mothers’ Level-1 intercept / slope. These potential interactions will determine whether baseline MVPA is similar between conditions and whether the potential change in MVPA across time is similar between conditions accounting for the couple variation. Second, the fathers vs. mothers’ coefficients will be statistically compared using the multivariate hypothesis testing procedure (e.g., to determine if the magnitude of change in the minutes of MVPA is the same for fathers and mothers). Third, the correlations among the fathers and mothers’ intercepts and slopes will be examined to determine, for example, whether the mothers’ baseline minutes of MVPA are significantly associated with their own change in MVPA and / or their fathers’ change in MVPA (and vice versa).

To address the second and third objectives / hypotheses concerning the motivational, health-related quality of life, and health-related fitness outcomes, the same analytical approach as outlined in relation to objective 1 will be used when examining the variables as outcomes. However, to examine whether the Theory of Planned Behavior (TPB) variables explain the potential MVPA differences between conditions (i.e., whether the TPB variables mediate the condition/MVPA relationship), the appropriate Level-1 mediation analysis approach [32, 33] will be used treating the TPB variables as time varying covariates [60] while accounting for the couple variation. Finally, the fourth objective / hypothesis (i.e., whether season, gender) potentially moderate the condition / outcome relationships) will be examined by including the time invariant covariates (e.g., gender) at level-2 of the hierarchical model (i.e., by creating cross-level interactions to predict the fathers/wives’ intercepts and slopes at Level-1) and the time varying covariates (e.g., motivation variables, season) at Level-1 of the model. The primary investigator and project coordinator will have access to the final trial data set.

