### Objectives

The primary research question is whether a theory-based condition (based on an adapted theory of planned behavior) can maintain or improve adherence to regular moderate/vigorous intensity physical activity among new parents when compared to those in the control condition at 6 months post intervention (8 months after the birth of their first child). We also will explore four secondary research questions including:Does the theory-based condition improve motivational, health-related quality of life, and health-related fitness outcomes among new parents when compared to those in the control condition at 6 months post intervention?Can group differences among new parents with regard to these motivational, behavioral, and health-related fitness outcomes be explained through a mediation model?Can motivational variables predict adherence?Is there a seasonal, initial physical activity status, mental health or gender difference across primary outcomes by assigned condition?

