### Hypotheses

We hypothesize that physical activity will be higher for parents in the theory-based condition in comparison to parents in the control condition after controlling for possible confounds. The effect may wane over time from the initial measurement period at 2 months after the onset of parenthood but all outcomes will remain significantly higher 6 months after intervention. For the secondary research questions we hypothesize that the theory-based condition will change salient underlying motives (theory of planned behavior constructs, self-regulation constructs) for physical activity because its basis is from the key results of our prior longitudinal trial of new parents [52] and past interventions among mothers [23]. Health-related physical fitness and quality of life will also be higher for this condition in comparison to the control condition. All outcomes will remain significantly higher at 6 months post-intervention in the theory-based condition compared to the standard physical activity education group. Improvements in both groups of mothers may occur due to recovery from pregnancy, but our hypotheses should still hold. The covariance of the assigned conditions (theory-based, standard) on adherence will be explained by changes in the salient underlying motives for physical activity (i.e., manipulation check). In turn, the covariance between these salient underlying motives and health-related outcomes will be explained by physical activity adherence among conditions. The approach will test Ajzen’s [1] theory of planned behavior adapted to include self-regulatory constructs as a bridge between good intentions and behavior [46]. Affective attitude and perceived behavioral control will predict intention, intention will predict self-regulation constructs of planning and self-monitoring, and these will predict adherence across conditions. As for seasonal or gender differences we hypothesize that there will be no differences, however, this question is exploratory because there is limited research at present.

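### One straight line per parent answers the 6-month question only if the treatment effect builds up linearly; otherwise the slope misstates the 6-month effect and the intercept shows an apparent baseline difference

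*Protocol article*

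**What the plan says.** Under Objectives, the protocol article compares the theory-based condition with control at one time point: "when compared to those in the control condition at 6 months post intervention (8 months after the birth of their first child". Hypotheses adds "The effect may wane over time from the initial measurement period at 2 months after the onset of parenthood", while still predicting higher outcomes at 6 months.

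The accelerometer is worn "at each time period (baseline, 6 weeks, 3 months, 6 months", and Justification of sample size also counts four occasions. Procedures places randomisation after the baseline week: "After the 1 week wear of accelerometers, participants are randomized at a 1:1 ratio to either intervention or control group".

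Analysis strategy gives each parent an intercept and "a Father linear trend (0 = baseline; 1 = 6 months), and a Mother linear trend with all coefficients set to random". At Level 2, "condition (0 = control; 1 = intervention) predicts the fathers’ Level-1 intercept / slope and the mothers’ Level-1 intercept / slope". Two interpretations are fixed. For the slope: "the linear trends represent the change in MVPA (or not) over the 6-month interval". For the condition terms: "These potential interactions will determine whether baseline MVPA is similar between conditions", together with whether the change over time is alike in the two arms. The primary model is given no curvature term, categorical time or explicit 6-month contrast.

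**The concern.** With one linear trend, the arms can differ only by a constant and a constant rate. An effect that appears by 6 weeks and then holds or fades does not fit that form. The fitted line spreads the misfit over both parameters: the slope is pulled away from the true 6-month change, and the intercept difference is pulled away from zero by visits made after randomisation.

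Two conclusions are at stake. The main test could understate or miss a real 6-month effect. The report could also describe a baseline imbalance that the model produced, in a trial whose baseline was measured before allocation.

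**Working it through.** **1. The plan's own figure.** Inputs from Justification of sample size: four occasions, 6 months, within-person variance 1.0, growth rate 1.0 (read here as slope variance τ), effect size .40, 200 couples. Power .80 and alpha .05 are stated only for the predictor analyses; they are assumed here, two-sided.

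Noncentrality = J·d²·τ / [4(τ + V)], with V = σ² / Σ(t − t̄)². For visits at 0, 1.5, 3 and 6 months, Σ(t − t̄)² = 19.69 and V = .0508. Noncentrality = 200 × .16 / (4 × 1.0508) = 7.61, so power is .78 on F(1, 198). Reading the frequency as four per month over six months gives .80. Recruitment is 200 / .75 = 267. The sample size therefore reproduces, for a linear slope effect.

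**2. What the model estimates.** Put the visits on the model's 0–1 scale as t = 0, .25, .5, 1. The article fixes only the end points, so the middle values are assumed from calendar time. With complete data and random intercept and slope, the estimated condition effects equal the least-squares line through the visit-by-visit differences d:

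- slope = Σ(t − t̄)d / Σ(t − t̄)², with t̄ = .4375 and Σ(t − t̄)² = .5469; visit weights −.80, −.34, .11, 1.03
- intercept visit weights .60, .40, .20, −.20

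So three post-randomisation visits feed the term that is read as the baseline difference.

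**3. Results for assumed profiles** (peak effect 1, true baseline difference 0):

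| Difference at the four visits | True 6-month effect | Slope | Baseline difference | Fitted 6-month value |
|---|---|---|---|---|
| 0, .25, .5, 1 (linear) | 1.00 | 1.00 | 0 | 1.00 |
| 0, 1, 1, 1 (held) | 1.00 | .80 | .40 | 1.20 |
| 0, 1, .75, .5 (halving) | .50 | .26 | .45 | .71 |

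Halving row: slope = −.343 + .114 × .75 + 1.029 × .5 = .26; intercept = .40 + .20 × .75 − .20 × .5 = .45; sum .71. The slope is too low and the fitted 6-month value too high.

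**4. Sensitivity to coding.** If the visits were coded as equally spaced (0, .33, .67, 1), the slope weights are −.9, −.3, .3, .9. The halving slope is then −.3 + .225 + .45 = .375, a shortfall of 25% instead of 49%. The held slope is .90.

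**5. Power illustration.** All assumed: one parent, 200 couples, total SD 1, compound symmetry with correlation ρ = .5, true 6-month effect .40 SD, two-sided 5%, SE = √(4·Var/200).

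- Slope: Var = (1 − ρ)/.5469 = .914, SE = .135. Linear build-up, slope .40: 84%. Held, slope .32: 66%. Profile .6/.5/.4, slope .263: 49%.
- Change from baseline to 6 months: Var = 2(1 − ρ) = 1, SE = .141, effect .40: 81% for every shape.
- Same contrast with condition removed from the intercept: Var = 1 − ρ² = .75, SE = .122: 90%.

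Compound symmetry has no slope variance, whereas the plan makes all coefficients random. With the article's own variances and a true 6-month difference of .40 × 6 = 2.4, the slope test has 79% (linear), 60% (held) and 29% (halving). The change contrast, with SE = √(4 × 38/200) = .872, has 79%. The ordering is the same.

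**The case against.** The strongest reply is that nothing in the article establishes a non-linear effect. Hypotheses says the effect may wane, not that it will, and counts this from a measurement that precedes randomisation. The trial aims to prevent a decline and gives boosters at 6 weeks and 3 months. If controls drift down while the intervention arm holds, the gap could widen steadily; the slope is then unbiased and slightly more powerful (84% against 81%). A linear growth contrast is a standard choice and matches the growth-model sample size. All this stands, and it makes the point conditional on shape.

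It does not remove the point. Waning is not needed: an effect reached by 6 weeks and fully held is also misfitted. The article fixes the trend and its interpretation, so this is a stated choice and not a detail left to an analysis plan.

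The 0/1 coding might suggest that only the first and last visits enter, which would avoid the misfit. But the article counts four occasions. Two visits would also give each couple four observations for four random coefficients plus a residual, which is not identifiable.

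Stronger conclusions that a reader might infer are not supported:

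- **The plan predicts waning, so the bias is certain.** It only allows waning and gives no trajectory.
- **The slope reverses the sign of a real 6-month effect.** The profile 0, 1, .5, 0 gives −.29, but its true 6-month effect is zero.
- **The effect is always understated.** That applies to the slope in these profiles; the fitted 6-month value errs upward.
- **False positives are inflated.** If condition has no effect at any visit, both differences are zero in expectation.
- **The 200 couples are miscalculated.** The figure reproduces for a linear effect; it does not cover other shapes.

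**Conclusion.** The point holds in conditional form. The two interpretations fixed in Analysis strategy are valid only for a treatment effect that builds up linearly, an assumption the article does not state and Hypotheses leaves open. For a held or halving effect, the slope recovers 80% or 51% of the true 6-month effect, and an apparent baseline difference of 40% to 45% of the peak effect appears. These sizes rest on assumed profiles, calendar-time coding and complete data; equal spacing makes them smaller. The power loss, from 81% for the contrast to 66% or 49% for the slope, rests on the assumed SD scale and correlation. Severity: should-fix, because the primary estimate does not reliably answer the primary question and the remedy uses data already planned.

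**What to change.** In the fixed part of the model, replace each parent's linear trend with indicators for 6 weeks, 3 months and 6 months, and let condition predict each indicator. Name the condition difference at 6 months, for mothers and for fathers, as the primary estimate. Keep the random intercepts and slopes only to model the within-couple covariance. Report the 6-week and 3-month contrasts and the linear trend as secondary; the contrasts address waning directly.

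Drop the reading of the intercept term as a baseline test. Optionally, remove condition from the intercepts, which is justified because randomisation follows the baseline measurement. This is a separate step: it is what raises power from 81% to about 90% under the assumptions above, and the indicators alone do not.

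The cost is revised wording, a few more fixed effects and about 3 points of power (81% against 84%) if the effect is exactly linear. No new data are needed.
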